### Losses to follow-up

Patients identified as having atrial fibrillation without any recorded contact with GPs during the follow-up period will be considered lost to follow-up. The proportion of patients lost to follow-up or with partly completed follow-up will be compared across groups.

### Sample size

Our sample size estimate was powered to detect a clinically important difference between groups for our primary outcome. We considered a 10% difference in the primary outcome to be clinically important. We assumed that 50% of patients with atrial fibrillation managed by GPs assigned to the control arm received anticoagulation; assuming a 50% use of anticoagulation in the control arm will produce a conservative (*i.e*., larger) sample size estimate. To detect a difference of 10% (*e.g*., 60% vs. 50%) in the primary outcome between intervention and control groups, with 80% power at the 5% level of significance, we would require 407 eligible patients per group in a trial in which the unit of randomisation is the patient [36].

As practices (clusters) were randomised, we needed to allow for the correlation between the outcomes of patients from the same cluster. We have inflated the sample-size estimate by the design effect (DEFF); DEFF = [1 + (*m *- 1)ρ], where *m *is the average number of patients per cluster and ρ is the intracluster correlation coefficient (ICC) that quantifies the amount of within-cluster correlation for the outcome of interest [37]. An estimate for the ICC for warfarin uptake in patients with atrial fibrillation recruited within general practice clusters is 0.029 [11]. We have conservatively chosen an ICC of 0.04 in recognition of the imprecision with which ρ is estimated. We estimate an average of 20 eligible patients with NVAF per GP will be identified. This estimate assumes an average of 350 eligible patients over the age of 65 per GP, a prevalence rate for NVAF in general practice of ~8.6% [38], that our computerised search strategy will identify 85% of patients with atrial fibrillation, and that 80% of patients will not refuse permission for an independent medical record audit. Based on previous experience of recruiting GPs [39], we expect to recruit an average of 1.25 GPs per practice, yielding an average sample size of 25 patients per practice (1.25 × 20). The estimated DEFF is 1.96 (*i.e*., [1 + (25 - 1)0.04]). Therefore, we require 798 patients per group (*i.e*., 407 × 1.96). Assuming 10% will die, move away during the study, or be lost to follow-up, our revised sample size is 887 per group. We therefore aimed to recruit 36 practices per group (*i.e*., 887 ÷ 25 patients per practice), 72 practices in total, and 90 GPs in total (72 × 1.25 GPs per practice). To further allow for 10% drop out at practice level, we aimed to recruit 40 practices per group (80 in total, or 100 GPs), yielding a total patient sample of 2,000 (100 GPs × 20 patients or 80 practices × 25 patients) or 1,000 per group.

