## Methods

### GP recruitment

All GPs located in our local region, South Western Sydney, were selected from a commercial database containing the contact details of GPs in active practice [20]. We restricted the population to GPs practicing with up to five other GPs to avoid large medical centres where GPs, practice staff, and patients are more likely to be itinerant. GPs were located within postal codes of the geographically defined regions, known as Local Government Areas (LGAs), of Fairfield (population 190,657), Campbelltown (population 149,071), Camden (population 53394), Bankstown (population 182,178), Liverpool (population 176,903), Canterbury (population 139,985), and Marrickville (population 77,141) [21]. GPs were mailed a prenotification letter advising them that researchers from the Faculty of Medicine of the University of New South Wales were offering the opportunity to participate in an education program about stroke prevention in general practice. The letter advised GPs that a research nurse would phone their practice to arrange a practice visit to explain the study in detail and obtain written consent. This professional development program was accredited by the peak professional body representing GPs in Australia (The Royal Australian College of General Practitioners).

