### General practitioner randomisation and allocation concealment

After patients had been contacted, GPs were randomised by a statistician external to the research project to ensure allocation concealment, into one of two groups: DESPATCH or a waiting-list control. All GPs sharing the same practice address (group practices) were randomised as one cluster and randomisation occurred on the same day for all GPs (October 13, 2009). GPs were first stratified by LGA. Within each stratum, they were then ranked by practice size (*i.e*., the number of patients contacted at baseline) before being randomly allocated into one of the two arms of the study using computer-generated random numbers. Block randomisation with a fixed block size of two was used to minimise the discrepancy in sample size at the individual level.

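### The design effect of 1.96 leaves out the variation in practice size that the plan's own average of 1.25 GPs per practice implies; with it, at least about 847 rather than 798 patients per group are needed, or about 822 if the GEE weights practices efficiently

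*Protocol article*

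**What the plan says.** The Sample size section starts from an individually randomised comparison of 50% with 60%, "with 80% power at the 5% level of significance", and concludes that "we would require 407 eligible patients per group". It inflates this by DEFF = 1 + (m − 1)ρ, where m "is the average number of patients per cluster". The ICC is 0.04, raised from a published estimate of 0.029 because that estimate is imprecise. For m, "we expect to recruit an average of 1.25 GPs per practice", at 20 eligible patients per GP, so m = 25. Hence "The estimated DEFF is 1.96" and a requirement of 798 patients per group. Allowing for 10% patient loss gives 887 patients, or 36 practices. Allowing for 10% practice dropout gives 40 practices.

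The article gives no measure of spread in practice size. Its randomisation section shows that sizes differ: GPs at one address form one cluster, and "Within each stratum, they were then ranked by practice size", size being the number of patients contacted at baseline. The planned analysis is a GEE with exchangeable correlation and robust standard errors, clustered on practice.

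**The concern.** The design-effect formula holds when clusters are equal in size. When they are not, large practices contribute many correlated patients, and the variance is larger than the mean size suggests. The plan's own inputs exclude equal sizes, because GPs come in whole numbers and the stated mean is 1.25. The formula therefore does not fit the clusters that the article describes, and 798 is too small by the plan's own method.

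What is at stake is the accuracy of the stated requirement and of the 80% power attached to it. Readers will use those figures to judge how informative a result near zero is, even though the article says it will interpret effects by their size and 95% confidence intervals.

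**Working it through.** **Inputs.** From the Sample size section: 50% v 60%, 80% power, 5% level (two-sided assumed, which reproduces the stated figure), ICC 0.04, mean 1.25 GPs per practice, 20 patients per GP, 10% patient loss, 10% practice dropout. The CV of practice size is not stated.

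**Plan's figures reproduced.** The continuity-corrected two-proportion formula gives 407.1 per group (387.3 without the correction). Then:
- DEFF = 1 + 24 × 0.04 = 1.96
- 407 × 1.96 = 797.7, so 798
- 798 / 0.9 = 886.7, so 887
- 887 / 25 = 35.5, so 36 practices
- 36 / 0.9 = 40 practices

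There is no slip in the arithmetic.

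**Smallest CV that the plan allows.** The most even whole-number split with mean 1.25 is 75% of practices with one GP and 25% with two. Its variance is 0.75 × 0.25 = 0.1875 and its SD 0.433, so CV = 0.433 / 1.25 = 0.346 and CV² = 0.12. This assumes exactly 20 patients for every GP. If patients per GP also vary independently, the CV is higher. For example, with an assumed between-GP SD of 10 (CV 0.5), the practice variance is 1.25 × 100 + 0.1875 × 400 = 200, the SD is 14.1, and the CV is 14.1 / 25 = 0.57.

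**Formulas with unequal sizes.**
- Without credit for weighting: DEFF = 1 + [(1 + CV²)m − 1]ρ.
- With an efficiently weighted exchangeable GEE: DEFF = [1 + (m − 1)ρ] / [1 − CV²·L(1 − L)], where L = m / [m + (1 − ρ)/ρ]. At m = 25 and ρ = 0.04, L = 25/49 = 0.510.

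At the floor, the first gives 1 + (1.12 × 25 − 1) × 0.04 = 2.08, and 407 × 2.08 = 846.6. The second gives 1.96 / (1 − 0.12 × 0.2499) = 2.021, and the requirement is 822.4.

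**Requirement, and power with 798 patients (ρ = 0.04, m = 25).** Figures in brackets use GEE weighting.

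| CV | DEFF | Patients per group | Power with 798 |
|---|---|---|---|
| 0 (plan) | 1.96 | 798 | 80.0% |
| 0.35 (floor) | 2.08 (2.02) | 847 (822) | 77.5% (78.7%) |
| 0.50 (assumed) | 2.21 (2.09) | 900 (851) | 74.8% (77.3%) |
| 0.65 (assumed) | 2.38 (2.19) | 970 (892) | 71.4% (75.2%) |

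**Power at the planned recruitment.** After 10% practice dropout, 36 practices remain. After 10% patient loss, each has 25 × 0.9 = 22.5 analysed patients, or 810 per group. This takes the CV as unchanged by losses. At the floor, DEFF = 1 + (1.12 × 22.5 − 1) × 0.04 = 1.968, and the effective size is 810 / 1.968 = 411.6, just above 407.

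| CV | 36 practices, 810 patients | 40 practices, 900 patients |
|---|---|---|
| 0.35 | 80.5% (81.5%) | 84.6% (85.5%) |
| 0.50 | 78.0% (80.1%) | 82.4% (84.3%) |
| 0.65 | 74.9% (78.1%) | 79.5% (82.5%) |

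**ICC.** With 36 practices and 810 patients:
- At the published 0.029, power is 86.0%, 84.2% and 81.9% at CV 0.35, 0.50 and 0.65 (86.6%, 85.5% and 83.8% with weighting).
- At an assumed 0.05, it is 75.5%, 72.6% and 69.0% (76.9%, 75.5% and 73.4% with weighting).

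**The case against.** The strongest reply is that the design has enough slack. At the only CV that can be derived from the article, 36 practices still reach 80% after both kinds of loss, and the exchangeable GEE recovers part of what unequal sizes cost. The ICC was set above its published estimate, the 50% control rate was chosen as conservative, and 407 includes a continuity correction. All of this stands as an account of likely power, and it rules out a flat statement that the trial is underpowered.

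It does not rescue the stated requirement. The higher ICC was justified by imprecision in the ICC and the extra practices by dropout; using either to cover unequal sizes spends a margin set aside for something else. The published-ICC figures show that the margin is large only if the published estimate is right.

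A reader might also infer a sixfold range of cluster sizes from "We restricted the population to GPs practicing with up to five other GPs". That sentence defines which practices are eligible. Clusters consist of recruited GPs, expected to average 1.25, so the floor of 0.35 rests on that mean and not on the eligibility limit.

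Finally, this is an article. But the point is not that a detail is missing: the article gives the formula, its inputs and the result in full, and the formula does not match those inputs.

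**Conclusion.** The point holds for the stated design effect and requirement. At ICC 0.04 and m = 25, the plan's own figures imply a design effect of at least 2.08 and about 847 patients per group, 6% more than 798 (2.02 and about 822, or 3% more, with efficient GEE weighting). With 798 patients, power is about 77.5% (78.7%).

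A reader might go further and conclude that 36 practices per group are too few. The article does not support that. At the floor CV, 36 practices give about 80.5% (81.5% with weighting). They fall clearly short, by more than about two points, only at CVs above about 0.5 (about 0.65 with weighting), or at an ICC above 0.04. Those values are assumptions. The weighted figures assume that the working correlation is close to the true one; the floor assumes 20 patients for every GP.

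**What to change.** Restate the design effect, the required number and the power with the CV term.

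- Take the CV from the audited eligible NVAF patients per practice once the audit is complete. Until then, use the patients contacted per practice, which were counted before randomisation. Label this as a proxy, since those contacted include everyone who met the age and medication search and not only patients with confirmed NVAF.
- Report power for 36 and 40 practices per group over a range of ICCs from 0.029 upward, marking values above 0.04 as assumptions.
- Give the figures with and without GEE weighting.

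This costs one recalculation and a slightly less favourable statement of power. Recruitment, randomisation and the planned analysis stay as they are.

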### Statistical analysis

All outcomes will be analysed according to the intention-to-treat principle, where patients are analysed according to the arm to which their practice cluster was allocated. Analyses of the outcomes will be implemented using marginal logistic regression models using generalised estimating equations (GEEs), with information sandwich ('robust) estimates of standard error to allow for within-cluster (within-general practice) correlation for dichotomous outcomes [40]. An exchangeable correlation structure will be specified for the marginal models using GEEs. Clustering will be accounted for only at the practice level as this is the unit of randomisation. Analyses will adjust for stratification of GPs by LGA.

In addition to unadjusted analyses, we will carry out adjusted analyses to allow for the effect of characteristics, current at the time of randomisation, as noted above.

Percentage of inter- and intrarater agreement and kappa coefficients will be calculated to quantify rates of reliability for the collected audit data [41].

Significance of the study results, specifically, the effect of the intervention on primary and secondary outcomes, will be ascertained by examining the magnitude of the estimated effect of the intervention and corresponding 95% CIs. When testing for interaction terms, a *p *value of < .05 will be used to determine significance of the effect. Analyses will be carried out blinded to group allocation.

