### Baseline comparisons between DESPATCH intervention and control groups

We will compare groups on key patient and practice characteristics current on the date of randomisation. Specifically, we will compare the DESPATCH and control groups on the numbers of patients identified with atrial fibrillation, patient sex, age (mean and median differences), CHADS2 scores (0, 1, 2+, and mean scores), use of oral anticoagulation current at time of randomisation (that is, up to three months before randomisation; yes or no), and whether patients were recruited from practices where one or more than one GP participated in the study.

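### Adjustment omits the practice-size ranking used in the randomisation, and neither the unadjusted nor the baseline-adjusted analysis is named as primary

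*Protocol article*

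**What the plan says.** All places are in the protocol article.

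- **Randomisation** (General practitioner randomisation and allocation concealment). Allocation was stratified by LGA. "Within each stratum, they were then ranked by practice size", where size means the number of patients contacted at baseline. Allocation then used fixed blocks of two, so practices adjacent in size within an LGA are in effect paired.
- **Model** (Statistical analysis). A logistic GEE with exchangeable correlation and robust standard errors, clustered by practice. The only design factor carried in is LGA: "Analyses will adjust for stratification of GPs by LGA".
- **Two analyses** (same section). "In addition to unadjusted analyses, we will carry out adjusted analyses to allow for the effect of characteristics, current at the time of randomisation". Since all analyses adjust for LGA, I read the unadjusted analysis as LGA only. No sentence ranks the two.
- **Covariates** (Baseline comparisons between DESPATCH intervention and control groups). The list includes "use of oral anticoagulation current at time of randomisation (that is, up to three months before randomisation; yes or no". The number of patients contacted per practice is not on it. The nearest items are the number of patients found to have atrial fibrillation and whether one or several GPs in the practice took part.
- **Target effect** (Sample size). "We considered a 10% difference in the primary outcome to be clinically important".

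**The concern.** Three things are left open or dropped.

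1. One of the two factors that shaped the allocation is missing from the analysis. If practice size is related to anticoagulation, a model that ignores the pairing overstates the standard error.
2. Baseline anticoagulation is likely to predict later anticoagulation well, because the follow-up indicators are the same kinds of record entry as the baseline ones. Whether that information counts depends on which of the two analyses is called the result, and the text does not say.
3. A logistic GEE gives an odds ratio. The odds ratio from the baseline-adjusted model is conditional on baseline use and will generally lie further from 1 than the unadjusted one, even for the same effect in percentage points. Two unranked analyses therefore give two different numbers, neither of them directly on the scale on which the trial defines clinical importance.

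At stake are power and a clear, prespecified primary result. The validity of the randomisation is not in question.

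**Working it through.** **1. The plan's own figure.** Inputs from Sample size: "We assumed that 50% of patients with atrial fibrillation managed by GPs assigned to the control arm received anticoagulation"; 60% against 50%; "with 80% power at the 5% level of significance, we would require 407 eligible patients per group"; "We have conservatively chosen an ICC of 0.04 in recognition of the imprecision"; 25 patients per practice. The 5% level is taken as two-sided.

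- Without continuity correction: [1.96√(2×0.55×0.45) + 0.8416√(0.50×0.50 + 0.60×0.40)]² / 0.10² = 1.968²/0.01 = 387.3, so 388.
- With continuity correction: (387.3/4)[1 + √(1 + 4/38.73)]² = 407.1, so 407 (408 if rounded up).
- Design effect 1 + 24×0.04 = 1.96; 407×1.96 = 798; 798/0.9 = 887.

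The plan's 407, 798 and 887 reproduce, with no credit taken for any covariate.

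**2. Baseline anticoagulation, risk-difference scale.** Let r be the correlation between baseline and outcome status, the same within and between practices. The documents do not give r; it is an assumption. The variance factor is 1 − r², and the effective sample per group is n = 798/[1.96(1 − r²)]. Power (no continuity correction) is Φ{[0.10 − 1.96√(0.495/n)] / √(0.49/n)}.

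At r = 0, n = 407.1 and Φ[(0.10 − 0.0683)/0.0347] = Φ(0.913) = 81.9%.

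| Assumed r | 1 − r² | Effective n | Power at 798 per group | Needed per group (408×1.96×(1 − r²)) |
|---|---|---|---|---|
| 0 | 1.00 | 407 | 82% | 800 |
| 0.3 | 0.91 | 447 | 85% | 728 |
| 0.5 | 0.75 | 543 | 91% | 600 |
| 0.7 | 0.51 | 798 | 98% | 408 |

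To judge r: with 50% treated at baseline and 50% at follow-up, r equals the proportion of baseline users treated later minus the proportion of non-users treated later. So 65% v 35% gives 0.3, 75% v 25% gives 0.5 and 85% v 15% gives 0.7.

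**3. Practice size.** Let q be the share of between-practice variance that size explains (assumed). Between-practice variance is 0.04/(0.04 + 0.96/25) = 0.04/0.0784 = 51% of the variance of a practice mean, so the variance factor is 1 − 0.51q.

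| Assumed q | SE factor | Power if size is in the model | True type I error if size is left out |
|---|---|---|---|
| 0.05 | 0.987 | 83% | 4.7% |
| 0.10 | 0.974 | 84% | 4.4% |
| 0.25 | 0.934 | 87% | 3.6% |
| 0.50 | 0.863 | 92% | 2.3% |

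**4. The planned logistic GEE, by simulation.** 32 practices per arm, 25 patients each, ICC 0.04, true rates 50% v 60%, q = 0.1, practices paired by size, LGA unrelated to outcome, 300 runs per setting. Entries are mean log odds ratio, mean SE and rejection rate.

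| r | LGA only | + size | + baseline use |
|---|---|---|---|
| 0.3 | 0.412, 0.139, 82% | 0.415, 0.135, 83% | 0.454, 0.141, 88% |
| 0.5 | 0.412, 0.139, 82% | 0.414, 0.135, 83% | 0.551, 0.149, 96% |
| 0.7 | 0.405, 0.140, 82% | 0.407, 0.136, 84% | 0.791, 0.169, over 99% |

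On the log-odds scale the SE does not fall when baseline use is added. The estimate moves further from zero, and the gain shows as power. With no true effect (r = 0.7) the three models rejected in 8% to 10% of runs, against a Monte Carlo SE of √(0.05×0.95/300) = 1.3 points. The rejection rates therefore serve only to compare models.

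**5. Effect scale.** The same 10-point effect gives an unadjusted odds ratio of about exp(0.41) = 1.51 and a baseline-adjusted one of exp(0.454) = 1.57, exp(0.551) = 1.73 or exp(0.791) = 2.21 at r = 0.3, 0.5 or 0.7. The control rate matters too: 60% v 50% is an odds ratio of (0.6/0.4)/(0.5/0.5) = 1.50, while 80% v 70% is (0.8/0.2)/(0.7/0.3) = 1.71.

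**The case against.** **Baseline adjustment is already planned.** This stands. A reader might infer that the LGA-only model is the main one and that the precision from baseline use is simply thrown away. The text names no main model. Power is lost only if the unadjusted result is later taken as primary.

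**The size of the gain is assumed.** This also stands. A reader might infer a 20% to 40% cut in the standard error, which is what r = 0.6 to 0.8 would give (factors 0.80 to 0.60). Nothing in the documents fixes r in that range, at r = 0.3 the gain is small, and the cut applies to the risk difference, not to the log odds ratio of the planned GEE.

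**Practice size was ranked to balance numbers, not because it is prognostic.** The protocol gives that purpose, and the likely cost is small and in the conservative direction. It remains a factor used in the allocation and absent from the analysis. The number of patients found to have atrial fibrillation is a related count, but not the one used for ranking.

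**Analysis is blinded.** Coded groups are supplied only after database lock, which limits choosing a result by its direction. It does not say which analysis is primary.

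**Odds ratios can be converted, and the reporting scale is often left to an analysis plan.** An odds ratio converts to a difference once a control rate is stated, so it would be wrong to say that it cannot be compared with 10 points. The comparison is indirect, and it differs between the two planned analyses.

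**Conclusion.** The point holds in a limited form. The stated models leave out a factor used in the randomisation. The unadjusted and baseline-adjusted analyses, which estimate different odds ratios, stand side by side without rank, and neither is directly on the 10-point scale.

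Taking the unadjusted result as primary would forgo about 3, 9 or 16 power points at r = 0.3, 0.5 or 0.7 (82% against 85%, 91% or 98%), given the plan's own rates, ICC, cluster size and 798 patients per group. Leaving out practice size probably costs 1 to 2 points (q = 0.1) and keeps type I error at or below nominal by the formula; it would matter only if size explained a large share of between-practice variance.

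The sample size does not depend on adjustment, so the trial is adequately powered on its own inputs either way. This is a cheap improvement and a needed clarification, not a flaw that invalidates the design.

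**What to change.** Before group codes are released:

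- Name one primary analysis: a GEE with arm, LGA, number of patients contacted per practice, and anticoagulation current at randomisation (yes/no), clustered by practice.
- Report from it a standardised (marginal) risk difference with a cluster-robust 95% CI, beside the odds ratio, so that the result can be read against the 10-point target.
- Keep the analysis without baseline anticoagulation (LGA and size) as supportive, and say so.

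The cost is a change of wording and one standardisation step. No new data are needed: the number contacted was known at randomisation, and baseline anticoagulation comes from the record audit that was under way when the article was written. The one drawback is that the adjusted odds ratio is conditional on baseline use and differs in meaning from the unadjusted one. The report should state this; the standardised risk difference does not have the problem.
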